### Patient Demographics and Characteristics

To describe patient demographics and presentation, we will report age, sex, education level, work status, marital status, referral source (primary care physician or orthopaedist), history of corticosteroid injection for the current episode, and prior participation in physical therapy for same or different diagnosis. Instruments to assess systemic and comorbidities include the Optimal Screening for Prediction of Referral and Outcome- Review of Systems (OSPRO-ROS) [48] and the Pain Catastrophizing Scale (PCS) [50, 51]. The OSPRO-ROS is a review-of-systems screening tool that includes constructs associated with comorbidities and systemic pathologies [55]. The PCS is a 12 item questionnaire ranking types of thoughts and feelings one has while in pain from 0 (not at all) to 4 (all the time) [50]. Table 4 details the psychometric properties of the OSPRO-ROS and PCS.

### Sample Size Estimate

We powered the study for proportional differences between conditions on decision to have surgery for up to 6 months. Using projections from previous data, and assuming offset inequity between two independent conditions; we modelled power on the following assumptions. In the absence of prior studies, the authors project 30 % of the impairment-based condition only to pursue surgery versus 5 % from the impairment-based plus PEERC condition. This assumes an allocation ratio of 1/1 and error of probability of 0.05 and projected power of 80 %. With these assumptions, our projected sample size requires 94 participants. We will employ intention to treat in the primary analysis and do not plan for dropouts.

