**Methods:**

We will test the effectiveness of the Patient Engagement, Education, and Restructuring of Cognitions (PEERC) intervention which is intended to change expectations regarding conservative care. The PEERC intervention will be evaluated in a randomized, pragmatic “add-on” trial, to better understand the effect the intervention has on outcomes. Ninety-four (94) participants with rotator cuff related shoulder pain referred for physical therapy will be randomized to receive either impairment-based care or impairment-based care plus PEERC. Both groups will receive impairment-based conservative treatment created by compiling the evidence associated with established, effective interventions. Participants assigned to the impairment-based care *plus* PEERC condition will also receive the PEERC intervention. This intervention, informed by principles of cognitive behavioral therapy, involves three components: (1) strategies to enhance engagement, (2) education and (3) cognitive restructuring and behavioral activation. Outcomes will be assessed at multiple points between enrolment and six months after discharge. The primary outcome is patient reported decision to have surgery and the secondary outcomes are pain, function, expectations and satisfaction with conservative care.

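### The stated inputs (30% versus 5%, error probability 0.05, 80% power, no dropout allowance) do not give 94 participants for the planned test; 94 gives about 87% to 93% power by the two tests named

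*Protocol article*

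**What the plan says.** The protocol article sizes the trial on the primary outcome, the patient-reported decision to have surgery. Under Sample Size Estimate, "the authors project 30 % of the impairment-based condition only to pursue surgery versus 5 % from the impairment-based plus PEERC condition". The design parameters follow: "This assumes an allocation ratio of 1/1 and error of probability of 0.05 and projected power of 80" per cent. The section then concludes: "With these assumptions, our projected sample size requires 94 participants". It closes with "We will employ intention to treat in the primary analysis and do not plan for dropouts".

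The Methods part of the abstract confirms that 94 is the total for both arms: "Ninety-four (94) participants with rotator cuff related shoulder pain referred for physical therapy will be randomized". The Statistical Analysis section names a chi-square test, or Fisher exact, of the difference in proportions as the primary analysis.

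Three further details bear on the calculation. The section says that power was modelled with an offset between the two independent conditions, but gives no value for it. It does not say whether the error probability is one- or two-sided. It does not name the test used for sizing.

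**The concern.** The section gives every input that a two-proportion sample-size calculation normally needs, and then a result, so the two should agree. They do not: the result is larger than the inputs imply by 8 to 22 participants. Dropout inflation, the usual reason for such a gap, is ruled out by the section's own last sentence.

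The stated power is what a reader uses to judge how much missing outcome data the trial can absorb. The primary outcome is collected by telephone six months after discharge, so some loss is plausible. As written, 80% power with no dropout allowance implies no margin, whereas the design does have one.

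**Working it through.** **Inputs.** From Sample Size Estimate: p1 = 0.30, p2 = 0.05, so d = 0.25; allocation 1:1; error probability 0.05; power 80%; no dropout; total 94, so n = 47 per arm. From Statistical Analysis: chi-square or Fisher exact against no difference. Assumed here: two-sided testing, because sidedness is not stated.

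**Pooled chi-square formula.** The mean rate is (0.30 + 0.05)/2 = 0.175.

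- Null term: √(2 × 0.175 × 0.825) = √0.28875 = 0.5374.
- Alternative term: √(0.30 × 0.70 + 0.05 × 0.95) = √0.2575 = 0.5074.
- n per arm = [(1.960 × 0.5374 + z × 0.5074)/0.25]², where z is the normal quantile for the power.

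At the stated 80% power (z = 0.842), n = 35.06, so 36 per arm and 72 in total. This does not reproduce 94. At 90% power (z = 1.282), n = 46.43, so 47 per arm and 94 in total.

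**Continuity-corrected formula.** n' = (n/4) × [1 + √(1 + 4/(n × d))]². With n = 35.06, n' = 42.7, so 43 per arm and 86 in total.

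**Fisher exact.** Summing the binomial probabilities of all tables with two-sided p ≤ 0.05, power is 79.2% at 38 per arm and 80.7% at 39. The requirement is therefore 39 per arm, 78 in total.

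**Other variants at 80% power.** The two-sided unpooled formula gives 66 and the arcsine formula 64. One-sided testing moves further from 94: 56 pooled, 72 with continuity correction.

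**Power with 47 per arm.**

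| Method (two-sided 0.05) | Total N for 80% power | Power at N = 94 |
|---|---|---|
| Pooled chi-square formula | 72 | 90.4% |
| Uncorrected chi-square, exact enumeration | – | 93.4% |
| Fisher exact, exact enumeration | 78 | 87.2% |
| Continuity-corrected formula | 86 | 84.5% |

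For the pooled row: (0.25 × √47 − 1.960 × 0.5374)/0.5074 = 1.302, and Φ(1.302) = 0.904. For the continuity-corrected row, 0.25 is replaced by 0.25 − 1/47, which gives 1.015 and Φ(1.015) = 0.845.

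**Margin for missing outcomes.** The pooled formula keeps at least 80% power down to 36 evaluable per arm: 1 − 72/94 = 23% loss. Exact enumeration of the uncorrected chi-square gives 85.1% there. Fisher exact has only 75.9% at 36 per arm and needs 39: 1 − 78/94 = 17% loss.

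**The offset.** A score test of H0: p1 − p2 = δ was enumerated at 47 per arm. Two-sided power is 81.0% at δ = 0.04 and 77.9% at δ = 0.05; one-sided power is 81.0% at δ = 0.07. These δ values are trial values, since the article gives none.

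**The case against.** The strongest reply is that the section mentions an offset. If the null hypothesis was a non-zero difference of about 0.04 (two-sided) or 0.07 (one-sided), 94 participants would give roughly 80% power, and both figures could be correct for the calculation that was run. This stands in part: it cannot be said that no calculation yields 94 at 80%. It does not clear the text. No offset value is given, and the primary chi-square or Fisher test is against zero difference. If an offset was used, the trial was sized for a hypothesis that it will not test.

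A reader might infer that the trial was really sized for 90% power and that 80% is a slip. The exact match of 94 to the pooled formula at 90% makes this tempting, but the document does not show it. Other routes reach 94 too: the continuity-corrected formula at 80% power gives 47 per arm for 30% versus 6%. The match is suggestive only.

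It is also fair that the direction is harmless. Every method tried against a null of no difference puts power at 94 above 80%. Patients, endpoint, test and type I error are unaffected, and what a non-significant result excludes is read from the observed confidence interval, not from the planning power. That argues for a modest rating, not for leaving the figure as it is.

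One adjacent wording issue carries no weight here. The section refers to "Using projections from previous data" and then says "In the absence of prior studies, the authors project" the two rates. The second phrase may mean only that no trial of this intervention existed.

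**Conclusion.** The point holds as a should-fix correction. For the planned test against no difference, at two-sided 0.05, the stated inputs need 72 (pooled chi-square), 78 (Fisher exact) or 86 (continuity-corrected) participants, not 94. With 94, the stated 80% is too low by about 10 points on the pooled formula (13 by exact enumeration), 7 for Fisher exact and 4.5 on the continuity-corrected formula.

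This rests on three assumptions: two-sided testing, a zero offset, and all 94 participants evaluable. One-sided testing with a zero offset would widen the gap. A non-zero offset could close it, but only by departing from the stated analysis. Which calculation the authors ran cannot be determined from the article.

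**What to change.** Keep 94 participants and reword the Sample Size Estimate section so that it can be reproduced:

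- State that 47 per arm give about 90% power by the pooled chi-square formula, or about 87% by Fisher exact, to detect 30% versus 5% at two-sided 0.05.
- State that at least 80% power is retained down to 36 evaluable per arm for chi-square, or 39 for Fisher exact. Give both, because the analysis allows either test.
- Name the test and the sidedness used for sizing.
- Remove the offset, or state its value and reconcile it with the zero-difference test in Statistical Analysis. If the original calculation did give 94 at 80% power, report the inputs that produce it.

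The cost is one reworded paragraph. No participants are added, and the design and analysis do not change unless the authors choose to keep a non-zero offset.

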### Statistical Analysis

We will evaluate descriptive statistics of the two conditions using appropriate parametric and nonparametric tests for differences, depending on the data (continuous or frequency based). For our primary outcome (patient-reported surgery or intention to have surgery), we will measure condition differences in proportions between the impairment-based care only shoulder treatment and the impairment-based care plus PEERC, using a chi-square analysis (or Fisher Exact).

For our secondary aims, we will use linear mixed effects modelling to compare pain (NPRS and SPADI), function (SPADI, GRoC, TEGNER, and SANE), and follow up expectations and satisfaction (MODEMS) between the two conditions. Linear mixed effects modelling methods are flexible, model individual change, and accommodate for missing data (when present). We will run two analyses, unadjusted and adjusted, in which we will control for all baseline characteristics that are significantly different (if present) and baseline patient expectation, functional outcome, and pain. Pain intensity measures will be evaluated using a negative binomial Poisson, which accounts for count variables with significant skew.

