### Randomization and Blinding

Consented participants are randomized to receive either the (1) impairment based care group or (2) impairment based care plus PEERC group (Fig. 2). Consecutively numbered, sealed, opaque envelopes containing group allocation were prepared by a researcher with no other involvement in the study. Condition allocation involves randomization within random permuted blocks using the random number function in Excel and is stratified according to treating therapist so that all physical therapists will deliver approximately equal numbers of patients in both conditions to control for therapist variation. Participants are blinded to study purpose of improving expectations of conservative care and decisions to pursue surgery. Rather than employ deceit, it is communicated that the investigators wish to improve the patient experience through additional education and interaction.

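### Secondary outcomes: extra covariates are chosen by testing baseline differences for significance, and the randomisation stratum (therapist) is in no stated model

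*Protocol article*

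**What the plan says.** All but the last two items come from the Statistical Analysis section of the protocol article.

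- **Baseline comparison.** "We will evaluate descriptive statistics of the two conditions using appropriate parametric and nonparametric tests for differences". No significance threshold is given.
- **Primary outcome.** Proportions in the two arms are compared once, by chi-square or Fisher's exact test, with no covariates.
- **Secondary outcomes.** Linear mixed models are planned for NPRS, SPADI, GRoC, TEGNER, SANE and the MODEMS scales. "We will run two analyses, unadjusted and adjusted", and in the adjusted one "we will control for all baseline characteristics that are significantly different (if present) and baseline patient expectation, functional outcome, and pain".
- **Candidates.** The section Patient Demographics and Characteristics lists eight demographic or history items and two instruments, OSPRO-ROS and PCS.
- **Stratum.** Under Randomization and Blinding, allocation uses permuted blocks and "is stratified according to treating therapist". Therapist is not mentioned in any analysis model.

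**The concern.** If the sealed-envelope randomisation works, the null hypothesis of every baseline test is true by construction. Such a p-value says nothing about bias. Nor does it say whether the variable predicts the outcome, which is the reason to adjust. Used as a selection rule, it can admit a variable that has nothing to do with recovery and leave out one that matters because it happens to be balanced.

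The additional part of the covariate list, and with it the standard error, is therefore not settled until the data are seen. The rule also cannot be reproduced as written, since neither the threshold nor the exact candidate list is given.

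Therapist was judged important enough to stratify on, yet is missing from the stated models. If outcomes differ between therapists, leaving the stratum out puts that variation into the residual and tends to make the standard errors for the treatment effect too large.

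At stake are the precision and reproducibility of the secondary comparisons, not the trial's main conclusion.

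**Working it through.** The plan gives no figure on this point to reproduce. The checks below measure how often the rule would act, and what it does to the test.

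**1. Inputs**

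- Candidates: age, sex, schooling, employment, marital status, source of referral, injection history and earlier physical therapy make 8. OSPRO-ROS and PCS bring this to 10.
- Test level: not stated; 5% assumed.
- Independence between candidates: assumed. Positive correlation would lower the chance of at least one entry somewhat, but not the expected number.
- Size: 94 participants, 47 per arm (Sample Size Estimate).

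**2. How often chance adds a covariate**

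P(at least one enters) = 1 − (1 − 0.05)^k; expected number = 0.05k.

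- k = 8: 1 − 0.95^8 = 0.337; expected 0.4.
- k = 10: 1 − 0.95^10 = 0.401; expected 0.5.

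Any one candidate stays out with probability 1 − 0.05 = 0.95, however well it predicts outcome.

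**3. Effect on the type I error**

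A simulation used 47 per arm, a normal outcome with no treatment effect, one baseline covariate and 10,000 runs. The Monte Carlo standard error near 5% is √(0.05 × 0.95 / 10,000) = 0.22 percentage points. The covariate–outcome correlations are assumptions.

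| Correlation | Unadjusted | Covariate fixed in advance | Adjusted only if baseline p < 0.05 | Either result may be claimed |
|---|---|---|---|---|
| 0.3 | 5.07% | 5.05% | 4.69% | 6.45% |
| 0.5 | 5.22% | 5.10% | 4.31% | 7.49% |
| 0.7 | 4.52% | 4.86% | 3.08% | 7.68% |

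The selection rule on its own is conservative: it does not create false positives. A covariate fixed in advance holds the nominal level. The simulation leaves out the three covariates that the plan already fixes. With those in the model, a further covariate would usually explain less, so its effect would be smaller than the higher-correlation rows suggest.

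**4. Which outcomes have a baseline value (Table 4)**

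- Baseline value collected: SPADI, NPRS, TEGNER, MODEMS-E.
- None: GRoC, SANE, MODEMS-S.

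The reference to a baseline functional outcome therefore needs an instrument named, above all for the second group.

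**5. Therapist as fixed or random effect**

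The Setting section puts the clinic's staff at over 30 physical therapists; how many take part is not stated. If 30 did, there would be 94 / 30 ≈ 3.1 participants each, and fixed effects would use 29 degrees of freedom. That favours a random effect.

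**The case against.** The strongest reply is that little of consequence depends on this clause, and much of that reply stands.

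- **A reader might infer that the trial's main result is open to covariate choice.** It is not. The rule sits in the paragraph on the secondary aims, and the primary outcome has its own unadjusted test.
- **A reader might infer that the whole covariate set is unknown in advance.** It is not. Expectation, function and pain always enter, and the Discussion treats pre-treatment expectation as the best predictor of function under conservative care. The loss of precision is therefore partial.
- **A reader might count the baseline scales as candidates too.** Adding TEGNER, SPADI, NPRS and MODEMS-E gives 1 − 0.95^14 = 51%. But these measure the constructs already forced into the model, so they should not be counted as chance entries.
- **A reader might say that the estimand shifts with the covariates.** In a linear model under randomisation, adding a main-effect baseline covariate does not change the treatment effect being estimated. It changes the precision and the particular estimate obtained.
- **A reader might infer inflated type I error from the two analyses.** The 6.5% to 7.7% arises only if either result may be claimed, and the document does not say that. The missing ranking is largely a detail that an analysis plan not shown here could supply.

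The selection rule does not fall to this reply. It is stated outright, so it is not a detail left to another document, and it is the wrong basis for choosing covariates.

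**Conclusion.** The point holds for the secondary outcomes only. The plan states a faulty rule for adding covariates on top of three well-chosen fixed ones. On the assumptions of about 10 independent candidates and a 5% test level, it adds at least one covariate by chance in about 40% of trials, with 0.5 expected. That figure measures how often chance alters the model; it is not a measure of bias. No false-positive inflation from the rule itself was found. The cost lies in precision and reproducibility, and in the omission of therapist, whose size cannot be computed because the document gives no between-therapist variance. The correction is worthwhile and cheap, but it does not bear on the primary conclusion.

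**What to change.** In the Statistical Analysis section:

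1. Delete the clause that admits characteristics by significance, and the baseline tests that feed it. Report baseline data by arm descriptively.
2. Keep expectation (MODEMS-E), pain and function as fixed covariates. Use the outcome's own baseline value where there is one, and baseline SPADI where there is none (GRoC, SANE, MODEMS-S).
3. Add treating therapist as a random effect, to limit the degrees of freedom used with 94 participants.
4. If wanted, name one or two items already collected and believed prognostic, such as referral source or symptom duration from the recorded onset date.
5. Name this adjusted model as the main secondary analysis and the unadjusted one as supportive.

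The cost is about two sentences and slightly more modelling work, with no new data. The price is that chance imbalance in an unlisted item is not adjusted for. Recruitment was still open when the article was written, so the change could be made before outcomes are compared between arms.

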### Data Collection and Management

Study data are managed using REDCap (Research Electronic Data Capture) [56] electronic data capture tools hosted by the study institution. REDCap is a secure, web-based platform designed to provide an interface for validated data capture and export of data to statistical packages. De-identified data, both from the secure electronic medical record as well as paper questionnaires, is entered into the REDCap instrument by study personnel. Ownership of the final dataset rests with the institution.

### Monitoring

Because this investigation presents less than minimal risk or psychosocial harm, an independent data monitoring committee is not required. Adherence to the impairment based treatment intervention will be monitored via checklist for treatment fidelity by non-treating study personnel. To enhance treatment fidelity, the study therapists underwent a formal training program, use a treatment manual to guide their sessions. Participant retention is promoted through contact between the physical therapist and the patient along with participant honorarium provided at the initial physical therapy evaluation and at the conclusion of ten weeks of active participation.

### Ethics and Financial Support

This trial has the approval of the Institutional Review Board of Duke University under protocol identification number Pro00088103. Unanticipated problems involving risks to participants or others; information that indicates an adverse change to the risks or potential benefits of the research; or a protocol departure that harmed participants or others or compromises the integrity of the research data require prompt reporting to the institutional review board. This study is externally funded by the Academy of Orthopaedic Physical Therapy. The role of this funding source is solely financial and not influential or contributory to design or interpretation of results. All results from the study will be submitted for publication in peer-reviewed scientific journals. Prior to publication, the authors expect to present the results at professional conferences. For all forms of publication, the authors must meet the four tenets of authorship set forth by the International Committee of Medical Journal Editors. The authors declare no competing interests.

## Discussion

This trial aims to measure effects of a novel PEERC intervention designed to change expectations of conservative care. In the primary analysis, the efficacy of PEERC will be assessed via participant report of their having had or have the intent to have surgery 6 months after finishing impairment-based care. In secondary analyses we will also investigate the effect of PEERC on pain, function, expectations and satisfaction with conservative care. Reliance on patient reported outcome measures, because they often lack evidence of validity, is a recognized limitation of clinical trials. Our primary outcome, pursuance of surgery, is no exception. The medical record can be queried, but this would only serve to verify the presence, not the absence, of planned or performed surgery because the patient may seek care outside of the study institution.

When considering the management decisions for RCRSP, clinicians, policy makers, and patients are faced with an intriguing dilemma. Despite higher risks/harms with surgical treatments, conservative treatments have similar outcomes [1–4]. The comparable results may be a reflection of a dedicated focus toward a biomedically oriented strategy [57]. Patient expectations (outside the biomedically oriented mechanisms associated with conservative and non-conservative treatment approaches) may also influence functional outcomes and the decision to pursue additional care options. This assumption is supported by studies that have identified the prognostic role of patient expectations across a variety of conservative and non-conservative care options [47, 58].

A patient-centered approach emphasizes patients’ treatment expectations - i.e. their desires, thoughts, and beliefs about treatment and its outcome [59]. Patient-centered models of care allow patients more control in directing their treatment and are a viable alternative method of enhancing treatment outcomes [60]. No studies of RCRSP have investigated the influence of brief, theory-based interventions for changing expectations about what treatment is appropriate/optimal when evidence suggests there is not an obvious choice based on superiority. Our study will focus on addressing patient expectations to understand that a conservative approach will provide a similar outcome to surgery, without unnecessary risks.

Despite recognition that patient expectations has a role in influencing functional outcomes and the decision to pursue surgical care in patients with RCRSP [8–10], there have been few studies designed to test interventions designed to change expectations [15, 16]. Research has shown that the best predictor of functional outcomes with a conservative approach are pre-treatment, patient expectations [15, 61]. Expectations (i.e. attitudes, thoughts, and beliefs) are malleable using methods rooted in cognitive-behavioral science that focus on education, engagement and cognitive restructuring.

If this innovative PEERC intervention is successful, the approach may provide the appropriate foundations that could be applied to other musculoskeletal disorders where there are viable conservative options to surgical care.

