PEERC Component	Defining Elements of the PEERC Intervention
**Patient Engagement**	The engagement approach uses motivational interviewing (a method that works on facilitating and engaging intrinsic motivation within the client in order to change behavior) and elicitation of thoughts and beliefs about the patient’s targeted expectations. The physical therapist uses behavioral interviewing methods to elicit information on thoughts, feelings, and behavior related to pain. The interaction focuses on the patients’ pain, how pain influences their lives, and their thoughts and beliefs about pain.
**Education**	The health coach emphasizes that pain is a complex, multidimensional experience that is affected by thoughts, feelings and behaviors as well as the important role that self-management plays in treatment. Educational methods are informed by the literature on health literacy and use simple diagrams and charts from a provided booklet to help patients understand the equivocal results of conservative and non-conservative interventions. The health coach also familiarizes patients with the current most recommended strategies for care, including any potential harms, a timeline of expectancy and recurrence rates.
**Cognitive Restructuring**	Cognitive restructuring involves learning how: (1) to recognize thoughts that are distorted, unrealistic and/or self-defeating; (2) to replace these thoughts with more rational, realistic, adaptive thinking [26]; and (3) to engage in behavioral activation assignments designed to reinforce more adaptive thinking. Home based strategies such as behaviorally testing negative thoughts via behavioral activation exercises (e.g. engaging in an activity the patient is capable of, but has been avoiding because of fear of pain) are assigned. A number of CBT methods are employed, including discussion of how thoughts, feelings, and actions affect and are affected by pain, and a review of prior session content and practices. The patient is encouraged to identify activities that the user tends to avoid, leading to discussions of how to change activities and the development of an individual plan to increase the fit between daily activities and personal goals.

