### Primary Outcome

Our primary outcome measure is patient report of the decision to pursue surgery. Since the “add on” intervention of our study included patient decision-making support options, education, and facts that were designed to influence expectations, we were interested in whether this approach truly influenced high-stakes patient decisions, such as pursuance of surgery. Prior surgical decision-making studies have used similar or Likert-based outcomes [27, 28]. We selected a question framed around the patient’s choice among treatment approaches, and included the binary question: “Have you had surgery or are you scheduled for surgery for the shoulder problem that you were treated for in physical therapy?” We will use telephone contact at 6 months after discharge from impairment-based care. Because patients may pursue surgery outside of the study institution, in which case a scheduled procedure would not be documented in the medical record, this direct contact will better serve to capture decision of surgical pursuance.

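### The primary outcome rests on self-report alone; the reason given for discounting the medical record argues against using it alone, not against adding it

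*Protocol article*

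**What the plan says.** The Primary Outcome section of the protocol article defines the endpoint by one binary question, "Have you had surgery or are you scheduled for surgery for the shoulder problem that you were treated for in physical therapy", and fixes when and how it is asked: "We will use telephone contact at 6 months after discharge from impairment-based care". The reason given is that surgery at another institution would not appear in the study institution's record, so "this direct contact will better serve to capture decision of surgical pursuance".

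The Discussion accepts that patient-reported outcomes are a recognised limitation and that this one is no exception. It then says that a query of the alternative source, the medical record, is possible, but that "this would only serve to verify the presence, not the absence, of planned or performed surgery".

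Three other places bear on the point:

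- Randomization and Blinding: "Participants are blinded to study purpose of improving expectations of conservative care and decisions to pursue surgery". Participants are told instead that the aim is a better patient experience through added education and interaction.
- Interventions and Table 2: only the PEERC arm receives six 30-minute telephone sessions, with a booklet used to "help patients understand the equivocal results of conservative and non-conservative interventions".
- Data Collection and Management: "De-identified data, both from the secure electronic medical record as well as paper questionnaires, is entered into the REDCap instrument".

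The article describes no record check of the primary outcome, no rule for reconciling the two sources, and no event defined by either source.

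**The concern.** The two sources fail in different ways. The call can miss surgery that the participant does not report. The record can miss surgery done elsewhere. The article treats the second failure as grounds for preferring the call and does not consider using both.

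This matters because the first failure could differ by arm. PEERC patients spend six sessions on content designed to change their beliefs about conservative care, and the study later asks them whether they had or booked an operation. If some who did answer *no*, the reported PEERC surgery rate falls in the hypothesised direction with no change in behaviour. Blinding to purpose reduces this risk. It protects only in part, because the content given to one arm hints at the preferred answer. Reaching every participant, or blinding the caller, would not remove an error that lies in the participant's own answer.

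**Working it through.** **Step 1: the logic.** Suppose a participant was operated on, or is booked, and answers *no*. The true state is surgery present. A source that can verify presence can contradict that answer; the ability to verify absence is not needed. Absence matters only if the record is the sole source, because an empty record cannot rule out surgery elsewhere. The stated limitation therefore rules out replacing the call with the record and leaves the combination open.

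**Step 2: inputs.**

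- From Sample Size Estimate: 94 participants, allocation 1:1, so 94 / 2 = 47 per arm; projected surgery 30% with impairment-based care alone and 5% with PEERC; error probability 0.05; power 80%.
- From Statistical Analysis: chi-square test, or Fisher exact.
- Assumed, because the documents give no figure: *f*, the share of PEERC patients with surgery done or booked who answer *no* (none do so in the other arm); and *r*, the share of those false answers that the record recovers.

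**Step 3: the plan's own figure.** The usual two-sided formula for two proportions, with mean proportion (0.30 + 0.05)/2 = 0.175, is

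n per arm = [1.960·√(2·0.175·0.825) + z_power·√(0.30·0.70 + 0.05·0.95)]² / 0.25².

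At 80% power it gives 36 per arm (72 in total); at 90% it gives 47 per arm (94). The stated 94 thus matches 90% power rather than 80%. That is a separate matter, and what follows uses only the 47 per arm.

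**Step 4: false-positive rate when PEERC has no effect.** Let the true surgery rate be p in both arms. The observed PEERC rate is

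p·[1 − f·(1 − r)],

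with r = 0 for self-report alone. For p = 0.30 and f = 0.20 this is 0.30 × 0.80 = 0.24; for f = 0.30 it is 0.30 × 0.70 = 0.21. The false difference is 6 or 9 percentage points. The chance of a significant two-sided chi-square (no continuity correction, 0.05) was found by summing the exact binomial probabilities of all significant outcomes at 47 per arm.

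| f (PEERC only) | Reported PEERC rate | Self-report alone | Record recovers 50% | Record recovers 80% |
|---|---|---|---|---|
| 0% | 30% | 5.1% | 5.1% | 5.1% |
| 10% | 27% | 6.3% | 5.4% | 5.2% |
| 20% | 24% | 10.0% | 6.3% | 5.3% |
| 30% | 21% | 16.9% | 7.8% | 5.5% |
| 50% | 15% | 41.6% | 13.0% | 6.3% |

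With p = 0.20, self-report alone gives 8.3%, 12.6% and 28.7% at f = 20%, 30% and 50%. With Fisher exact and p = 0.30, it gives 6.6% and 11.8% at f = 20% and 30%, from a base of 3.1%.

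**Step 5: single outcomes.** Take 14 events in the control arm (0.30 × 47 = 14.1).

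| PEERC events | Chi-square p | Fisher p |
|---|---|---|
| 7 | 0.083 | 0.136 |
| 6 | 0.044 | 0.076 |
| 5 | 0.021 | 0.038 |
| 4 | 0.009 | 0.017 |

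From 14 against a true 7, one false *no* reaches significance by chi-square and two by Fisher. From 14 against a true 14, it takes eight by chi-square (14 against 6) or nine by Fisher (14 against 5). That is 8/14 = 57% or 9/14 = 64% of the PEERC patients with surgery.

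**The case against.** **The limitation is disclosed, and direct contact is well justified.** This stands. The article gives a valid reason for the call and names self-report as a limitation. The issue is narrower: the reason offered does not bear on using both sources.

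**The article may condense a fuller protocol that has a verification step.** This stands in part. The text says that the record can be queried and does not say that it will not be. A reader might infer that the sponsor has ruled out any check; the documents do not go that far. The article does, however, argue for self-report over the record, and that argument can be judged as it stands.

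**Nothing shows that patients deny surgery.** This stands. The question concerns a concrete fact rather than an attitude, and participants are not told the surgery hypothesis. A reader might infer that blinding must fail in the PEERC arm and that those patients will answer to please the study. The intervention content makes that possible; no passage establishes it.

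**A few false answers decide the result only in a middle range.** This stands. Starting from 14 against 7 assumes a true halving of surgery, so misreporting there exaggerates a real difference and does not create one. At the planned 5% (2 or 3 PEERC events against 14), Fisher p is already 0.002 to 0.006, so further under-reporting would not change the conclusion.

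**An either-source rule could bias against PEERC.** This stands for a rule that counts every booking made after randomisation. A patient who books and then cancels would count as an event, although the true answer to the study's question is *no*. Changing such decisions is what PEERC aims to do, so reversals could be more common in that arm. The rule must follow the status of the booking at the call.

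**Conclusion.** The concern holds as a weakness in how the primary outcome is ascertained, not as a demonstrated bias. The reason for discounting the record does not support leaving it out, since verified presence is what corrects a false *no*. With no true effect, 30% surgery in both arms and 47 per arm, an assumed 20% to 30% of false *no* answers confined to PEERC raises the chi-square false-positive rate from about 5% to 10–17%. A record check that recovers half of them lowers this to 6.3–7.8%; one that recovers 80%, to 5.3–5.5%. At f = 10% the inflation is slight (6.3%).

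These figures rest on assumed values of *f* and *r* and on under-reporting in one arm only. They do not support the inference that the trial's result will be false, or that two or three wrong answers could turn no effect into a significant one.

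**What to change.** Keep the telephone question. Add a query of the institution's medical record for every participant in both arms, done in the same way by someone without access to allocation. Count a primary event if any of these holds:

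1. the participant answers *yes*;
2. the record shows surgery on the index shoulder performed between randomisation and the call;
3. the record shows such surgery scheduled and not cancelled as of the call date.

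Fix the rule before any outcome data are analysed by arm. Report self-report alone beside it, and tabulate the discordant cases by arm. If the registered primary outcome is not to be changed while the trial is running, keep it and report the either-source version as a prespecified sensitivity analysis.

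The cost is about 94 chart queries in a record that already supplies study data, plus an amendment if the primary definition changes. The correction is partial, because surgery outside the institution is still caught only by self-report.
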